## 6.6. Outcomes

### *Effectiveness*

Main outcome: time (days) from intubation to extubating.

- Secondary outcomes:

- Days free of mechanical ventilation until day 28
- Days of delirium until day 28
- Time in ICU with delirium until day 28
- Days of hospitalization with delirium until day 28
- Days of sedation until day 28
- Sedation-free days until day 28
- Extubating failure
- Need for non-invasive mechanical ventilation
- Exploratory outcomes:
- Barthel index at discharge
- Days of hospital stay
- Length of stay in ICU
- Mortality from any cause up to 90 days
- Time from intubation to start of therapy
- Muscular strength measured with the Medical Research Council (MRC) scale
- Dysphagia 72 hours after extubation
- Dysphonia 72 hours after extubation
- Time until initiation of oral administration post-extubation
- Development of healthcare-associated pneumonia,
- Maximum mobility measured by JH-HLM
- Grip strength
- Cognitive function measured using the Montreal Cognitive Assessment (MOCA)
- Evaluation of functionality in daily activities until day 28
- Quick sensitivity and dexterity test

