| Comparator | Late multimodal therapy is defined as the initiation of multimodal therapy 3 days or more after the start of mechanical ventilation. The comparator differs from the study intervention only in the moment (time from orotracheal intubation to the start of multimodal therapy) of initiation of therapy.                                                                                                                                                                                                                                                                                                                                                                                                                                                                                                                                                                                                                                                                                                                                      |
| Outcomes   | 
Effectiveness
 
Primary outcome: Number of days with invasive mechanical ventilation in the ICU
 
Secondary outcomes:
 
 
• Days free of mechanical ventilation until day 28
 
• Days of delirium until day 28
 
• Time in ICU with delirium until day 28
 
• Days of hospitalization with delirium until day 28
 
• Sedation days until day 28
 
• Sedation-free days until day 28
 
• Barthel index at discharge
 
• Days of hospital stay
 
• Length of stay in ICU
 
• Mortality from any cause up to 90 days
 
• Time from intubation to start of therapy
 
• Muscle strength measured with the medical research scale council (MRC)
 
• Dysphagia at 72 hours
 
• Time until initiation of oral administration
 
• Development of healthcare-associated pneumonia,
 
• Maximum mobility measured by JH-HLM
 
• Grip strength
 
• Extubation failure
 
 |

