**Exclusion Criteria:**

Patients requiring invasive mechanical ventilation through a tracheostomy cannula or nasotracheal tube

Patients who have undergone any type of head and neck surgery

Cardiac arrest

Airway burns

Burns covering more than 50% of the body surface area

Patients with chronic obstructive pulmonary disease (COPD)

Patients referred from another institution

Demyelinating diseases or neuromuscular junction disorders

Patients requiring neuromuscular relaxation

Patients with a life expectancy of less than 180 days

Patients who, by medical criteria, would not benefit from multimodal treatment

Patients not admitted to the ICU for the first time

Patients participating in other rehabilitation clinical trials

Patients with liver or kidney transplants

Patients who have undergone cytoreductive surgery (Sugar-Baker)

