## 6.7. Measurements

Within the framework of the protocol, measurements will be conducted at six key moments of the research: upon admission to the intensive care unit, during observation in the intensive care unit, at the start of ventilatory support weaning, post-extubation, upon hospital discharge, and at the end of the observation period. Additionally, continuous measurements of outcomes associated with the safety of the intervention will be performed.

Upon admission, crucial details about each patient will be collected, such as name, identifier code, medical record number, sex, and ethnicity. Health and functionality aspects will also be evaluated, including the Barthel Index and Body Mass Index. Diagnostic information will be complemented with the ICD-10 code, study group (early vs. late), and the unit of admission (surgical, neurological, septic and respiratory, cardiovascular, or burn unit). Severity scores such as SOFA, APACHE II, and SAPS II will be incorporated, along with temporal data such as admission date, discharge date, and the time elapsed from intubation to the start of therapy. Regarding respiratory parameters, fundamental variables at the time of intubation will be detailed, such as tidal volume, respiratory rate, PEEP, plateau pressure, static lung compliance, driving pressure, airway resistance, and the PaO2/FIO2 ratio.

During the observation phase, a rigorous daily patient evaluation process will be implemented to ensure accurate recording of their progress. Key variables will be monitored, such as days on mechanical ventilation (recording start and end dates), ventilator-free days, days with delirium (indicating start and end dates), days of hospitalization with delirium, and days of sedation (with details of start and end dates). The duration of mechanical ventilation, the possible need for tracheostomy, the presence of adult respiratory distress syndrome, and the eventual occurrence of healthcare-associated pneumonia will also be documented.

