| Grip strength at the time of extubation | Grip strength of the dominant hand within 24 hours after extubation                                                                                   | Continuous Quantitative | Kilograms

It will be 0 if the patient dies. |
| Failed extubation                       | Inability to breathe spontaneously in the first 48 hours after removal of the artificial airway and the patient is unable to maintain a patent airway | Qualitative Nominal     | Yes or no                                          |
| NIV POS extubation                      | Post-extubation non-invasive ventilatory support within 48 hours                                                                                      | Qualitative Nominal     | NOT = 0

IF = 1                              |
| Prolonged mechanical ventilation        | Invasive mechanical ventilation longer than 14 days                                                                                                   | Qualitative Nominal     | Yes or no                                          |
| Tracheostomy                            | Need to use a tracheostomy tube.                                                                                                                      | Qualitative Nominal     | Yes or no                                          |
| Adult respiratory distress syndrome     | Bilateral alveolar infiltrates with a PAFI less than 300.                                                                                             | Qualitative Nominal     | Yes or no                                          |

|                              |                                                                                                                   |                     |                                                                                                                                                                                                                                                    |
|------------------------------|-------------------------------------------------------------------------------------------------------------------|---------------------|----------------------------------------------------------------------------------------------------------------------------------------------------------------------------------------------------------------------------------------------------|

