### 6.13. Statistical Analysis Plan

A Shapiro-Wilk test will be conducted to verify the distribution of quantitative variables, considering the number of patients included. Data will be presented as means or medians, accompanied by their standard deviation or interquartile range, as appropriate. Categorical variables will be described as absolute and relative frequencies.

To compare continuous variables between the two groups (early vs. late therapy), a T-test or the Mann-Whitney U test will be employed, depending on the distribution of the data. For categorical variables, a  $\chi^2$  test or Fisher's exact test will be used, as appropriate.

The primary objective of the study is to evaluate the association between the use of early multimodal therapy and the days of invasive mechanical ventilation. To address this question, we will perform a survival analysis and a Cox regression. A risk variable will be created by combining the time of invasive mechanical ventilation and extubation (yes/no). Then, a univariable Cox regression analysis will be performed with the risk variable as the dependent variable and the intervention group (early vs. late) as the independent variable. Additionally, a survival curve will be generated, and differences between the two groups will be analyzed using a log-rank test.

To evaluate factors related to the time of mechanical ventilation, univariable Cox regression models will be performed for all variables included in the study. To determine whether continuous variables can be evaluated continuously or as categorical variables, the assumption of linearity will be checked through the Martingale residual plot. If linearity is not met, the variable will be stratified, and cut-off points will be defined according to the appearance of the plot. Subsequently, those variables with a statistically significant p-value (less than 0.25) and clinically important variables (age, sex, delirium, etc.) will be included in a multivariable Cox regression model. The best model will be selected through a Backward Stepwise process based on Akaike (AIC) and Bayesian (BIC) information criteria.

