Variables that could act as confounding factors will be evaluated through a second multiple regression model. In this model, the potentially confounding variable will be removed, and the resulting slope or estimator (adjusted estimate) will be calculated. If there is a change greater than 15%-20%, the confounding variable will be included in the final model. Otherwise, the most parsimonious model will be chosen.

To evaluate the interaction between two variables, another regression model will be performed, including a new variable resulting from multiplying the two potentially interacting variables. If the regression coefficient of this new variable has a significance level of less than 0.05, it is concluded that there is an interaction, and this variable will be included in the model. Variables with potential interaction will be identified by evaluating confounding factors. Researchers will also evaluate clinical variables that may be considered as interaction or confounding variables through the above-described strategy.

The assumption of proportional hazard will be evaluated using Schoenfeld residuals, and influential values will be analyzed through residuals versus observations plots. Multicollinearity will be assessed through matrix curves.

Logistic regression models will be used to assess the relationship between our dichotomous variables, such as failed extubation, post-extubation NIV, prolonged mechanical ventilation, tracheostomy, and dysphonia, and the other studied variables. The assumptions of a logistic regression model, such as linearity in the log of the odds, independence of errors, homogeneity of variance, absence of multicollinearity, absence of outliers, and proportionality of effects, will be evaluated through residual analysis and graphical diagnostics, such as Pearson residual analysis or deviance residual analysis.

A multiplicity adjustment strategy will be employed in statistical tests, such as the Bonferroni method, Holm-Bonferroni, or other methods that control the false discovery rate (FDR), to maintain the overall type 1 error rate at an acceptable level.

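### The primary event is extubation while the outcome is days of invasive ventilation; they diverge for a patient converted to tracheostomy, whose liberation through the cannula would never count as an event

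*Protocol*

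**What the plan says.** The endpoint and its event are stated in more than one form.

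- Protocol 6.6: "Main outcome: time (days) from intubation to extubating".
- Protocol 6.13: "A risk variable will be created by combining the time of invasive mechanical ventilation and extubation (yes/no"). This is the dependent variable of the univariable Cox model that answers the primary objective, shown alongside a survival curve with a log-rank test. The Summary repeats it.
- Protocol section 3, PICOT table: "Primary outcome: Number of days with invasive mechanical ventilation in the ICU".
- Protocol 6.11, variable table: ventilation days are days of invasive ventilation. Ventilator-free days are 28 minus that number, set to zero for death or ventilation beyond 28 days.

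Tracheostomy at entry is excluded (6.2: "Patients requiring invasive mechanical ventilation through a tracheostomy cannula or nasotracheal tube"). Tracheostomy after entry is foreseen. Section 6.7 lists "The duration of mechanical ventilation, the possible need for tracheostomy, the presence of adult respiratory distress syndrome" among the items documented during ICU observation. Section 6.11 carries a yes/no variable defined as "Need to use a tracheostomy tube". Section 6.13 names it among the logistic-regression outcomes: "such as failed extubation, post-extubation NIV, prolonged mechanical ventilation, tracheostomy, and dysphonia". Conversion is neither a withdrawal criterion in 6.2 nor a listed reason for discontinuing therapy, and analysis is by intention to treat (6.1), so these patients stay in. Annex 5 collects ventilation start and end dates, and tracheostomy as yes/no. Nothing says how a converted patient enters the primary variable.

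**The concern.** For a patient who keeps the endotracheal tube until the ventilator is withdrawn, the end of intubation and the end of invasive ventilation are the same moment. At tracheostomy they separate: the orotracheal tube comes out and invasive ventilation can go on through the cannula. A yes/no extubation flag then has no category for the patient who is later liberated through the cannula.

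These are plausibly among the longest-ventilated patients. That is an inference; the protocol gives neither a rate nor a timing. Censoring them would be informative, because conversion follows from difficulty in weaning. Treating staff know the allocation (6.1), so a coding rule left open could be settled after allocation is known. At stake are the estimated number of ventilation days, which is the general objective, and agreement between the primary outcome and ventilator-free days within one patient.

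**Working it through.** **1. One patient under each rule.** Assume intubation on day 0, tracheostomy on day 10 and end of invasive ventilation on day 20.

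| Rule | Time | Event? | Consequence |
|---|---|---|---|
| PICOT and 6.11 ventilation days | 20 | not defined | ventilator-free days 28 − 20 = 8 |
| 6.13, extubation = no | 20 | no, censored | days right, liberation lost as an event |
| 6.6, tube removal = extubation | 10 | yes, on day 10 | event scored with 10 ventilated days to come; would imply 28 − 10 = 18 ventilator-free days, not 8 |
| End of invasive ventilation, any airway | 20 | yes, on day 20 | all definitions agree |

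**2. Which coding the text favours.** The exclusion in 6.2 treats ventilation through a cannula as invasive ventilation. The time component in 6.13 is invasive ventilation time. Section 6.7 ties extubation to an assessment of whether withdrawal of support will be tolerated. Section 6.11 judges failed extubation after the artificial airway has been removed. The ventilation standard in Annex 1 links extubation with the patient breathing unaided. Together these favour coding a converted patient as not extubated, but none defines it.

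**3. Effect on an arm's mean if the clock stops at tracheostomy.** Inputs: 37 per arm (6.3: 31 + 6). Assumed conversion rate 5% to 15%, so 0.05 × 37 = 1.85 (about 2) to 0.15 × 37 = 5.55 (about 6) patients. Assumed 10 uncounted days each. Shift = 10 × n / 37.

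- n = 2: 20/37 = 0.54 days
- n = 4: 40/37 = 1.08 days
- n = 6: 60/37 = 1.62 days

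The yardstick is the planning difference in 6.3, 6.1 − 3.4 = 2.7 days. Conversions in both arms partly cancel: 4 in one and 2 in the other give a net 20/37 = 0.54 days. If time runs to the end of ventilation, as 6.13 says, this shift does not arise.

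**4. Effect on the planned test.** A simulation assumed 37 per arm, lognormal times with medians 3.4 and 6.1 days, and tracheostomy for everyone still ventilated on a common day. Each of 1,500 datasets per scenario was analysed under all codings.

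| Log-SD | Day | Converted, early / late | Power: any-airway event | Power: tracheostomy as event | Power: censored | Mean difference: true → clock stopped |
|---|---|---|---|---|---|---|
| 0.6 | 10 | 3.6% / 20.2% | 96.7% | 97.0% | 97.0% | 3.22 → 2.30 |
| 0.6 | 14 | 0.9% / 8.3% | 96.6% | 96.9% | 96.7% | 3.25 → 2.82 |
| 0.9 | 10 | 11.3% / 29.3% | 74.4% | 73.6% | 74.0% | 4.16 → 1.89 |
| 0.9 | 14 | 5.7% / 17.7% | 72.7% | 72.9% | 73.2% | 4.02 → 2.46 |

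Power moves by at most 0.8 points (74.4% to 73.6%). The censored coding was run with censoring on the conversion day. Running time to the end of ventilation gives the same log-rank result here, because nobody ventilated past that day can then have an event and the earlier risk sets are unchanged. Conversion on different days in the two arms was not simulated.

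**The case against.** A reader might infer that the protocol counts tracheostomy as successful extubation, so that an arm with more or earlier tracheostomies looks better by some 40% of the planning difference (1.08/2.7). The documents do not support that. The passages in step 2 make it the less natural reading. The 40% places four conversions in one arm and none in the other, with assumed rates and days. It also describes a shift in a mean, whereas the planned test is Cox with log-rank. If the slower-weaning arm has more conversions, a stopped clock shrinks the difference, as in the table.

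It is also fair that, under the natural coding, recorded days match the PICOT outcome and only the event flag is at fault; that late conversions change only the latest event times; and that section 6.7 speaks only of a possible need, in a population with several difficult-weaning groups excluded.

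Finally, censoring rules are often left to a separate analysis plan, which may exist. That does not dispose of the point. This protocol itself fixes the event as extubation, in 6.6 and 6.13, and names a different quantity in section 3 and 6.11. Applied literally, its rule gives a patient liberated through a cannula no event.

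**Conclusion.** The event and the outcome are defined inconsistently, and the inconsistency bites only for patients converted to tracheostomy after randomisation. The likely result is that they are censored and their liberation is never counted. Scoring the event at tracheostomy is possible from the wording of 6.6 but less natural.

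The size is unknown because no tracheostomy rate is given. Under the assumptions above, the log-rank test is little affected: about 1 power point or less, for a conversion day common to both arms. Estimated days could be off by about 0.5 to 1.6 in one arm's mean, but only if the clock stops at tracheostomy, and less in the between-arm difference if both arms have conversions. If few of the 74 patients are converted, the effect is small. The point warrants correction because the remedy is nearly free and removes a coding choice by unblinded staff; it does not show that the primary comparison would fail.

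**What to change.** In 6.6, 6.13 and the Summary, define the primary event as the end of invasive mechanical ventilation through any airway, endotracheal tube or tracheostomy cannula. Take it from the ventilation start and end dates already recorded under 6.7 and Annex 5. State that conversion to tracheostomy is neither an event nor a reason for censoring. Use the same end date for ventilation days and ventilator-free days in 6.11, so that these agree with the PICOT table.

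The cost is wording only. No patients, visits or procedures are added, and the calculation in 6.3 is not affected because it is based on mean days. A tracheostomy date in Annex 5 is optional and not needed for the primary endpoint. The change concerns outcome coding alone and touches no clinical decision about tracheostomy.

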### *Safety*

- Outcomes:

- Number of adverse events.
  - Altered blood pressure
  - Cardiac arrhythmia
  - Oxygen desaturation
  - Pain or agitation
  - Invasive line removal

- Gastrointestinal (nausea, vomiting or diarrhea)
- Tachypnea
- Altered neurological status
- Number of serious adverse events
- Unscheduled extubation
- Healthcare-associated pneumonia
- Bronchoaspiration

## 6.7. Measurements

Within the framework of the protocol, measurements will be conducted at six key moments of the research: upon admission to the intensive care unit, during observation in the intensive care unit, at the start of ventilatory support weaning, post-extubation, upon hospital discharge, and at the end of the observation period. Additionally, continuous measurements of outcomes associated with the safety of the intervention will be performed.

Upon admission, crucial details about each patient will be collected, such as name, identifier code, medical record number, sex, and ethnicity. Health and functionality aspects will also be evaluated, including the Barthel Index and Body Mass Index. Diagnostic information will be complemented with the ICD-10 code, study group (early vs. late), and the unit of admission (surgical, neurological, septic and respiratory, cardiovascular, or burn unit). Severity scores such as SOFA, APACHE II, and SAPS II will be incorporated, along with temporal data such as admission date, discharge date, and the time elapsed from intubation to the start of therapy. Regarding respiratory parameters, fundamental variables at the time of intubation will be detailed, such as tidal volume, respiratory rate, PEEP, plateau pressure, static lung compliance, driving pressure, airway resistance, and the PaO2/FIO2 ratio.

During the observation phase, a rigorous daily patient evaluation process will be implemented to ensure accurate recording of their progress. Key variables will be monitored, such as days on mechanical ventilation (recording start and end dates), ventilator-free days, days with delirium (indicating start and end dates), days of hospitalization with delirium, and days of sedation (with details of start and end dates). The duration of mechanical ventilation, the possible need for tracheostomy, the presence of adult respiratory distress syndrome, and the eventual occurrence of healthcare-associated pneumonia will also be documented.

In the weaning initiation phase, attention will focus on a series of key parameters to assess the patient's ability to discontinue mechanical ventilation. Detailed data will be recorded, such as the Delta POCC, reflecting the variation in vital capacity during a cough cycle, muscle pressure, P0.1 representing the pressure in the first 0.1 seconds of inspiration, the amount of secretions through the orotracheal tube, the asynchrony index, negative inspiratory force (NIF), leak percentage, peak cough flow, and specific measurements related to diaphragmatic capacity, such as excursion and thickness. These data provide a comprehensive view of respiratory functionality during the weaning

**Association between early multimodal therapy and days of mechanical ventilation in the intensive care unit of the Fundación Santa Fe de Bogotá: A randomized controlled clinical trial.**

Version 6.0

Fundación Santa Fe de Bogotá

April 8, 2024

process, allowing informed decision-making about the feasibility of withdrawing mechanical ventilation.

Before the extubation process, critical data will be collected to assess the patient's readiness and minimize potential risks. The Delta POCC, muscle pressure, P0.1, the number of secretions through the orotracheal tube, the asynchrony index, NIF, leak percentage, peak cough flow, diaphragmatic excursion, and thickness will be recorded. Additionally, the OMAHA score at the time of extubation will be documented, indicating the presence or absence of this event.

The decision to extubate a patient, according to the OMAHA+ Scale, is based on a comprehensive evaluation of various clinical parameters. Each component of this scale provides crucial information about the patient's ability to tolerate the withdrawal of ventilatory support. When all factors described in the OMAHA+ Scale are present, extubation is performed.

The systematic application of the OMAHA+ Scale is fully standardized in our unit, forming an essential part of our extubation protocol. This ensures a thorough and uniform evaluation of patients before withdrawing ventilatory support. Additionally, we have implemented a systematic review procedure of the process to strengthen the consistency, accuracy, and quality of our clinical practice.

The OMAHA+ Scale is detailed below:

1. Oxygenation (O): The PaO2/FiO2 ratio > 150, arterial oxygen saturation > 90% with FIO2 0.4, PEEP ≤ 8 cm H2O and Tobin's index (fr/Vt) < 105. Each variable will be marked as yes or no.
2. Respiratory Mechanics (M): exhaled tidal volume greater than 5 ml/kg vital capacity > 10 ml/kg, maximum inspiratory pressure (MIP) ≤ -20 to 25 cmH2O, respiratory rate < 35 per minute, and values of PIM and PEM.
3. Acid-Base (A): paCO2 < 50 mmHg, pH > 7.32, lactic acid > 2, and venous saturation > 75%.
4. Hemodynamic (H): Systolic pressure > 90 or < 160, heart rate ≤ 140 per minute, the presence of arrhythmias and doses of vasopressors (high > 0.2 mcg (kg/min)
5. Airway (A): history of difficult airway and leak test results > 40%.
6. Clinical Component (+): Additional clinical factors, such as the presence of effective cough, management of secretions, the patient's neurological status, resolution of the underlying cause of intubation, and the manifestation of clinical signs of respiratory distress, as well were considered.

After extubation, several indicators will be carefully monitored to assess the patient's recovery and stability. The presence of dysphonia at 72 hours, maximum mobility measured by JH-HLM at 24 hours, and grip strength within the same period will be recorded. Additionally, the need for non-invasive mechanical ventilation at 48 hours will be evaluated, indicating whether it is required or not. The possible presence of dysphagia at 72 hours will also be documented, along with the timing of oral intake initiation, classified into two options: 1) between 12 and 24 hours, and 2) after 24 hours. The occurrence of extubation failure at 48 hours will be recorded, indicating whether

it occurred or not, and muscle strength will be measured using the MRC Scale at 24 hours to assess the patient's functional capacity after the extubation procedure.

After the observation phase, essential data related to the patient's functionality and hospital stay will be collected. The Barthel Index at hospital discharge, cognitive function measured by the Montreal Cognitive Assessment (MOCA), and the quick sensitivity and dexterity test will be recorded, providing a detailed measure of the functional and cognitive capacity achieved. Additionally, the days of hospital stay and the length of stay in the Intensive Care Unit (ICU) will be documented, offering insights into the duration of the recovery process. Mortality will be evaluated, indicating whether it occurred during the observation period. Furthermore, functional independence will be measured using Activities of Daily Living (ADLs) at hospital discharge and ICU discharge, providing a comprehensive assessment of the impact of care and procedures on the patient's autonomy (see Annex 3 and 4).

Within the protocol, the inclusion of safety variables such as blood pressure alteration, cardiac arrhythmias, and oxygen desaturation highlights the importance of continuous monitoring of cardiovascular and respiratory health in patients. These variables serve as key markers to identify potential complications during the intervention or medical treatment. Early detection of blood pressure alterations provides crucial insights into perfusion and circulatory function. Monitoring cardiac arrhythmias aims to identify irregularities in heart rhythm while observing oxygen desaturation alerts to potential issues in tissue oxygenation. These safety measures, integrated into the protocol, contribute to a comprehensive evaluation and proactive management of any changes in the patient's condition, thereby supporting safety and well-being during the clinical process.

[figure not shown]

**Figure 1.** Study design diagram

